### **18.5 Tolerability Analysis (adverse events)**

Tolerability analyses will be performed on the Safety Population only.

#### **18.5.1 Adverse Events**

Adverse Events will be coded using the Medical Dictionary for Regulatory Activities (MedDRA) central coding dictionary.

#### **18.5.2 Serious Adverse Events**

Serious Adverse Event reconciliation will be performed by Data Management, Clinical Research, and Pharmacovigilance via data listings.

A summary of patients with serious adverse events will be presented by treatment group for all patients in the Safety Population. A data listing of SAEs will also be provided, displaying details of the event(s) captured on the CRF. The between group difference will be tested using Chi-square test or Fisher's exact test.

#### **18.5.3 All Adverse Events**

Summaries of patients with AEs by System Organ Class and Preferred Term (MedDRA) will be prepared. Each patient will be counted only once within each category (System Organ Class or Preferred Term). If a patient experiences more than one AE within a category, only the AE with the strongest relationship or the greatest intensity, as appropriate, will be included in the summaries. The between group difference will be tested using Chi-square test or Fisher's exact test. Only AEs beginning at or after the beginning of study drug administration will be included.

### **18.6 Adjustment for Covariates and Subgroup Analyses**

In addition to the primary and secondary analyses adjusting for age, baseline NIHSS score, pre-stroke mRS, baseline ASPECTS score, the use of intravenous thrombolysis, time from onset to randomization, and occlusion location, exploratory analyses will be conducted to determine the potential roles of common baseline characteristics and assess potential heterogeneity of treatment effect across subgroups. The primary pre-specified subgroups as follows will be explored.

- age
- sex
- baseline NIHSS score
- pre-stroke mRS
- baseline ASPECTS score
- intravenous thrombolysis

- time from last known well to randomization. (mins)
- occlusion location
- Complete Reperfusion defined as Extended Thrombolysis in Cerebral Infarction grade 2c or 3
- Patients with any radiological haemorrhages
- Patients with symptomatic haemorrhages

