## 9.2 Exclusion Criteria

Patients meeting any of the following criteria will be excluded from study enrolment.

- Intracranial hemorrhage confirmed by cranial computed tomography (CT) or magnetic resonance imaging (MRI);
- mRS score  $\geq 2$  before onset;
- Pregnant or lactating women;
- Allergic to contrast agents;
- Allergic to glucocorticoids;
- Participating in other clinical trials;
- Systolic blood pressure  $> 185$  mmHg or diastolic pressure  $> 110$  mmHg, and oral antihypertensive drugs can not control;
- Genetic or acquired bleeding constitution, lack of anticoagulant factors; Or oral anticoagulants and INR  $> 1.7$ ;
- Blood sugar  $< 2.8$  mmol/L (50 mg/dl) or  $> 22.2$  mmol/L (400 mg/dl), platelet  $< 90 \times 10^9/L$ ;
- The artery is tortuous so that the thrombectomy device cannot reach the target vessel;
- Bleeding history (gastrointestinal and urinary tract bleeding) in recent 1 month;

- Chronic hemodialysis and severe renal insufficiency (glomerular filtration rate < 30 ml/min or serum creatinine > 220 umol/L [2.5 mg/ dL]);
- Life expectancy due to any advanced disease < 6 months;
- Follow-up is not expected to be completed;
- Intracranial aneurysm and arteriovenous malformation;
- Brain tumors with imaging mass effect;
- Severe systemic infectious diseases.

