#### **14.1.2 Randomization (R)**

If all inclusion criteria are met and no exclusion criteria are present, randomization will be performed.

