## **15.3 Safety Analysis-Primary Endpoint**

### **15.3.1 Primary Safety Endpoints**

- Mortality due to any cause at 90 (±7) days;
- Proportion of patients with symptomatic intracranial haemorrhage within 48 hours after endovascular treatment. Symptomatic intracranial haemorrhage will be adjudicated by an independent Imaging Core Laboratory and the Clinical Events Committee according to the modified Heidelberg Bleeding Classification, and is diagnosed based on a combination of: 1) clinical deterioration, 2) imaging findings, and 3) causal relatedness assessment. Clinical deterioration is defined as any of the following conditions: 1) NIHSS score increased more than 4 points than that

immediately before worsening; 2) NIHSS score increased more than 2 points in one category; 3) Deterioration led to intubation, hemicraniectomy, external ventricular drain placement or any other major interventions. The imaging criteria are presence of parenchymal hematoma type 2 (PH2), parenchymal hematoma type 1 (PH1), remote intracerebral haemorrhage (RIH), subarachnoid haemorrhage (SAH), intraventricular haemorrhage (IVH), or subdural haemorrhage. When clinical deterioration and PH2 co-occur, the event is automatically categorized as SICH. When clinical deterioration and PH1/RIH/SAH/IVH/SDH co-occur, the event is deemed SICH if it is judged that the haemorrhage contributed substantially to the clinical worsening. When clinical deterioration occurs only with haemorrhagic infarction type 1 or 2 (HI1 or HI2), the event is automatically classified as not SICH. ICH.

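### Section 18.6 lists two post-randomisation haemorrhage outcomes as treatment-effect subgroups; their estimates can be biased by selection if the drug changes who bleeds

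*Supplement*

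**What the plan says.** Section 18.6 of Protocol 2.0 gives its aim as follows: "exploratory analyses will be conducted to determine the potential roles of common baseline characteristics", and to look for heterogeneity of treatment effect. It continues "The primary pre-specified subgroups as follows will be explored". The list begins with true baseline factors (age, sex, baseline NIHSS, pre-stroke mRS, ASPECTS, thrombolysis, time to randomisation, occlusion site). It ends with three items of another kind: "Complete Reperfusion defined as Extended Thrombolysis in Cerebral Infarction grade 2c or 3", "Patients with any radiological haemorrhages" and "Patients with symptomatic haemorrhages". The section gives no time window for haemorrhage, no caveat, and no method for groups formed after randomisation.

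Elsewhere haemorrhage is handled as an outcome. Section 15.3.1 makes it a primary safety endpoint: "Proportion of patients with symptomatic intracranial haemorrhage within 48 hours after endovascular treatment". Section 15.3.2 makes any radiologic haemorrhage within 48 hours of treatment a secondary safety endpoint. Section 18.4 compares both between arms in the Safety Population.

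**The concern.** A subgroup comparison keeps the protection of randomisation only if treatment could not have influenced membership. Here the drug may influence it. Section 4.3 credits corticosteroids with stabilising the blood-brain barrier in animal models, and Section 4.2 names haemorrhagic transformation as a harm of reperfusion. If the drug prevents or causes bleeds, those who bleed under methylprednisolone are a different selection of patients from those who bleed under placebo, and the same holds for those who do not bleed. The result is selection (collider) bias.

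What is at stake is how the subgroup results are read. A figure for patients who bled, carrying the label of a primary pre-specified subgroup and standing beside age and NIHSS, could be taken as a treatment effect in an identifiable kind of patient. It need not be one, and bleeding status is unknown when treatment is chosen.

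**Working it through.** **Timing.** Section 18.6 gives none, so it has to be inferred.

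- Section 9.2 excludes intracranial haemorrhage seen on CT or MRI.
- Section 14.1.2 says "If all inclusion criteria are met and no exclusion criteria are present, randomization will be performed". A correctly enrolled patient therefore has no haemorrhage at baseline.
- Sections 15.3.1 and 15.3.2 count both haemorrhage types within 48 hours of EVT or treatment. Section 14.2.2 places the follow-up scan 48 to 96 hours after study drug.

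Both groups therefore form after randomisation.

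**Inputs for size.** The plan gives no haemorrhage rate, so there is no figure of its own to reproduce on this point. Two numbers are taken from Section 18.1: control mRS 0-2 = 7% + 20% + 16% = 43%, and 836 patients per arm. Everything else is assumed. In both illustrations the drug has no effect on mRS.

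**Illustration 1: two equal prognostic strata.** Assumed control haemorrhage risk is 15% (good prognosis) and 55% (poor), 35% overall. Assumed mRS 0-2 is 63% and 23%, 43% overall. Let the drug cut haemorrhage by 5 points in each stratum.

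- Placebo, bled: (0.5×0.15×0.63 + 0.5×0.55×0.23)/0.35 = 0.1105/0.35 = 31.6% good outcome.
- Drug, bled: (0.5×0.10×0.63 + 0.5×0.50×0.23)/0.30 = 0.0890/0.30 = 29.7%.
- OR with haemorrhage = (0.2967/0.7033)/(0.3157/0.6843) = 0.91.
- Without haemorrhage: placebo (0.43 − 0.1105)/0.65 = 49.2%, drug (0.43 − 0.0890)/0.70 = 48.7%, OR 0.98.

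Other assumed effects on haemorrhage:

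| Drug effect on haemorrhage | OR, bled | OR, did not bleed |
|---|---|---|
| None | 1.00 | 1.00 |
| −3 points in each stratum | 0.95 | 0.99 |
| −10 points in each stratum | 0.80 | 0.97 |
| 30% relative cut in both | 1.00 | 0.91 |
| 10% relative cut in low-risk, 50% in high-risk | 1.23 | 0.84 |

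Size and direction depend on how the drug changes bleeding.

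**Illustration 2: continuous frailty.** U ~ N(0,1), T = 1 for drug. logit P(haemorrhage) = b0 + bu·U + log(OR_h)·T, and logit P(good) = −0.35 − bo·U, with no T term. b0 is set for 35% haemorrhage on placebo. Rejection rates are for a two-sided 5% test on crude log odds ratios at 836 per arm.

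| bu, OR_h, bo | Haemorrhage on drug | OR, bled | OR, did not bleed | Ratio | Reject, bled | Reject, did not bleed | Reject, interaction |
|---|---|---|---|---|---|---|---|
| 0.8, 0.7, 1.0 | 28.2% | 0.96 | 0.96 | 0.99 | 5.7% | 6.2% | 5.0% |
| 1.2, 0.6, 1.5 | 26.4% | 0.90 | 0.92 | 0.98 | 8.4% | 11.3% | 5.1% |
| 1.5, 0.5, 2.0 | 24.5% | 0.82 | 0.87 | 0.95 | 14.3% | 22.5% | 5.6% |

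With OR_h = 1 every odds ratio is 1.00 and every rejection rate 5.0%.

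For symptomatic haemorrhage (b0 = −3.2, bu = 1.2, OR_h = 1.6, bo = 1.5) the rate goes from 6.7% to 9.8%. The OR among those with symptomatic haemorrhage is 1.06, with an approximate 95% interval of 0.46 to 2.47 at this trial's size and rejection in 5.2%.

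**The case against.** The best case for leaving the list alone has four parts.

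- **The analyses are exploratory.** No alpha, power or confirmatory claim rests on them. The primary mRS analysis, the secondary analyses, the sample size and the between-arm haemorrhage comparisons do not depend on them. This stands and limits the severity.
- **The bias is conditional.** It needs a drug effect on haemorrhage. The documents describe blood-brain barrier stabilisation in animals; they name haemorrhagic transformation as a harm of reperfusion, not as a stated drug target. This also stands. A reader might infer that these subgroup effects are certain to be biased, and the documents do not support that. Nor can the condition be assumed away, because the safety endpoints exist to test it.
- **False effect modification is not shown.** A reader might infer that the interaction test would mislead. In the frailty model both strata shift almost equally and the test rejects 5.0% to 5.6% of the time. The uneven case in Illustration 1 (1.23 against 0.84) shows that divergence is possible under other assumptions, no more. Section 18.6 itself specifies no interaction test or reporting rule, and model detail is deferred to a SAP that is not among the documents reviewed.
- **Reperfusion grade is different.** A reader might put it on the same footing. It is not a trial endpoint, no passage says that the drug changes it, and it bears on the aim in Section 4.3 of helping patients after successful recanalisation. It can still post-date randomisation: eligibility needs only a decision for EVT (Section 9.1), and Sections 13.4 and 13.4.1 recommend a first dose within 15 minutes of randomisation and before arterial access closure. That warrants a label, not removal.

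None of this makes haemorrhage a baseline characteristic, and Section 18.6 presents it among them without comment.

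**Conclusion.** Wrong as written, minor (should-fix). The two haemorrhage items are post-randomisation safety outcomes placed in a list whose stated purpose concerns baseline characteristics. That conclusion rests on the exclusion rule and the 48-hour endpoint definitions, not on any assumed number.

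The size of the bias does rest on assumptions. In the frailty model the within-stratum odds ratios run from 0.82 to 0.96 with haemorrhage and from 0.87 to 0.96 without, for a drug with no effect on disability. False-positive rates reach 14.3% and 22.5% only in the most extreme setting. The shift for symptomatic haemorrhage is too small to detect in this trial. There is no bias in these models if the drug leaves haemorrhage unchanged. The primary analysis and the trial's main conclusion are unaffected.

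**What to change.** - Remove the two haemorrhage items from the Section 18.6 list of treatment-effect subgroups. Keep haemorrhage as an outcome, which Section 18.4 already provides, so no safety information is lost.
- If a mechanistic question remains, report it separately as a labelled post-randomisation, mediation or principal-stratum analysis. State its assumptions and give it no effect-modification reading.
- Keep the eTICI 2c/3 subgroup, with a note that the grade may be determined after randomisation.

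The cost is two deleted list items and one or two added sentences. Sample size, data collection and the primary analysis do not change.

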## **18.7 Missing data handling**

All efforts will be made to minimize the amount of missing data. However, some missing data may be inevitable due to, for example, loss to follow-up. Missing baseline covariates will be imputed using simple imputation or multiple imputation methods (Details in SAP Section 9.2.2). Sensitivity analyses based on different hypotheses about the missingness pattern of the primary outcome will be performed to test for the robustness of the primary analysis (Details in SAP Section 12.1.5).

## **19. Ethical and regulatory consideration**

### **19.1 General requirements and Considerations**

This study followed the ethical principles of the Helsinki Declaration. Approval of the conduct of the trial will be obtained from the Ethics Committees of all participating centres as well as from the local regulatory authorities. The trial will not start in any centre before written approval and authorization by the respective Ethics Committee and Regulatory Authority. Any subsequent protocol amendment will be submitted to

the Ethics Committee for approval. The involvement of committees in the clinical trial of MARVEL will further ensure that the subjects have the highest priority at any time. In addition to the treatment to be tested, all diagnostic procedures and treatments applied are part of standard management of acute stroke patients and will follow the national guidelines. These procedures are therefore of immediate benefit to the patients. The investigators will assure that every patient participating in the trial will receive best medical treatment.

## **19.2 Study monitoring and quality control**

The design of the MARVEL trial has been carefully reviewed and approved by the Steering Committee before being submitted to the Ethics Committees and Regulatory Authorities for approval. In addition, the independent EAB and DSMB and an external SAB have reviewed and approved the trial protocol and will continuously monitor the conduction of the trial. These committees, composed of well-known independent experts, will ensure sufficient alertness to all ethical and safety issues.

The investigators promise to conduct the MARVEL trial in accordance with this trial protocol, International Conference on Harmonization-GCP (ICH-GCP) Guidelines and applicable regulatory requirements. The investigators agree to provide reliable data and all information required by the trial protocol in an accurate and legible manner according to the instructions provided.

The investigators of this clinical trial is responsible to the health authorities and takes all reasonable measures to ensure the correct implementation of the clinical trial

protocol in terms of ethics, clinical trial protocol compliance, and the completeness and validity of the data recorded on the CRF.

The main responsibility of the monitoring team is to help investigators to ensure that all aspects of clinical trials are highly ethical, scientific, professional and standardized. The monitoring team will regularly contact the centres through field visits, emails or phone calls, and send inspectors to assess the progress of the trial, the compliance of investigators and patients with the trial protocol, and to resolve urgent issues. During these inspection visits, the inspector will work with the on-site investigator. The main aspects of inspection and monitoring are as follows (not exclusive): patient informed consent, patient recruitment and follow-up, serious adverse event recording and reporting, study drug supply, treatment compliance of study drug group participants, study drug count, concomitant treatment and data quality.

### **19.3 Informed Consent**

The written informed consent must be obtained from all participants in the clinical trial prior to inclusion into the study. Informed consent forms must be written to be easily understood by the participants or their legal representatives, enabling them to understand the purpose of the trial, procedures, possible benefits, potential risks, and the rights/obligations of participation. Participants have the right to withdraw from the study at any stage of the trial. Each participant must leave contact information to the investigator of the coordinating centre. At the same time, the investigator must leave

his own phone number to the participant so that the participant can find the investigator at any time.

#### **19.4 Confidentiality**

Personal data will be processed in accordance with Chinese data protection directives and regulations, relevant international legislation and good practices. Data will only be processed for the trial's purposes. The investigators encode each patient participating in the study by assigning a unique patient identification number to maintain confidentiality standards. This means that all individual patients' data will be linked to the CRF via a unique identification number throughout the trial. Individual patient's medical information will be recorded only in anonymous form. The clinical monitors may inspect source data in order to ensure the accuracy of the data recorded in the CRF.

#### **19.5 Liability and Insurance**

The study investigators provide an appropriate insurance for patients in the event of any trial related damage in accordance with applicable national laws. A certificate of insurance will be provided to the investigator of the coordinating centre in which this document is required.

### **20. Administrative procedures**

#### **20.1 Curriculum vitae**

A latest copy of the curriculum vitae of each investigator and co-investigator will be provided to the responsible coordinating centre prior to the start of the study.

## **20.2 Secrecy agreement**

The investigators will take all necessary measures to ensure that there is no violation of confidentiality in respect of all information accumulated, acquired or deduced in the course of the trial, other than that information to be disclosed by law.

## **20.3 Ownership of data and use of the study results**

All materials, information and unpublished documentation supplied to the investigators, inclusive of this study, and the patient case report forms are the exclusive property of the study initiators. Therefore, the study initiators reserve the right to use the data of the present study, either in the form of case report forms, or in the form of a report, with or without comments and with or without analysis, in order to submit them to the health authorities.

## **20.4 Protocol amendments**

Any protocol amendments will be prepared by the investigators. Protocol amendments should be submitted to the REB/IRB for approval prior to implementation in accordance with local regulatory requirements. Approval must be obtained from the REB/IRB and regulatory authorities (as locally required) before implementation of any changes, except for changes necessary to eliminate an immediate hazard to patients or changes that involve logistical or administrative aspects only

## **21. Data Retention**

The double reviewed case report form (CRF) and imaging data will be sent to the data management group. The person in charge of the data management group will check and sign the receipt form. The CRF will be kept by the research centre after data entry is completed.

## **22. Study report and publications**

The results of the trial will be reported to the regulatory authorities and ethics committees. The investigators will provide an annual safety report and the final report.

According to the pre-defined analysis in the clinical trial protocol, the results of the trial will be published in the appropriate journal (for manuscripts) or meeting (for abstracts).

By signing the clinical trial protocol, the investigator agrees that the results of the clinical trial can be used for publication.

The trial will be registered at the Chinese Clinical Trial Registry website.

## 24. Appendices

### 24.1 Appendix 1: mRS

Subject ID \_\_\_\_\_  
Subject Date of Birth \_\_\_\_/\_\_\_\_/\_\_\_\_  
Hospital ID \_\_\_\_\_  
Date of Examination \_\_\_\_/\_\_\_\_/\_\_\_\_

#### The Modified Rankin Scale (mRS)

(Use web calculator at [www.modifiedrankin.com](http://www.modifiedrankin.com) )

- 0 No symptoms
- 1 No significant disability; able to carry out all usual activities, despite some symptoms
- 2 Slight disability; able to look after own affairs without assistance, but unable to carry out all previous activities
- 3 Moderate disability; requires some help, but able to walk unassisted
- 4 Moderately severe disability; unable to attend to own bodily needs without assistance, and unable to walk unassisted
- 5 Severe disability; requires constant nursing care and attention, bedridden, incontinent
- 6 Dead

|----------------------------------------------------------------------------------------------------------------------------------------------------------------------------------------------------------------------------------------------------------------------------------------------------------------------------------------------------------------------------------------------------------------------------------------------------------------------------------------------------------------------------------------------------------------------------------------------------------------------------------------------------------------------------------------------------------------------------------------------------------------------------------------------------------------------------------------------------------------------------------------------------------------------------|--------------------------------------------------------------------------------------------------------------------------------------------------------------------------------------------------------------------------------------------------------------------------------------------------------------------------------------------------------------------------------------------------------------------------------------------------------------------------------------------------------------------------------------------------------------------------------------------------------------------------------------------------------------------------------------------------------------------------------------------------------------------------------------------------------------------------------------------------------------------------------------------------------|---------------------------|
| 
6. Motor Leg: The limb is placed in the appropriate position: hold the leg at 30 degrees (always tested supine). Drift is scored if the leg falls before 5 seconds. The aphasic patient is encouraged using urgency in the voice and pantomime, but not noxious stimulation. Each limb is tested in turn, beginning with the non-paretic leg. Only the case of amputation or joint fusion at the hip, should the examiner record the score as untestable (UN), and clearly write the explanation for this choice.
                                                                                                                                                                                                                                                                                                                                                                                            | 
0 = No drift; limb holds 90 (or 45) degrees for full 10 seconds.
 
1 = Drift; limb holds 90 (or 45) degrees, but drifts down before full 10 seconds; does not hit bed or other support.
 
2 = Some effort against gravity; limb cannot get to or maintain (if cued) 90 (or 45) degrees, drifts down to bed, but has some effort against gravity.
 
3 = No effort against gravity; leg falls to bed immediately.
 
4 = No movement.
 
UN= Amputation or joint fusion; explain: _____
 
6a= Left Arm.
 
6b= Right Arm.
                                                                                                                                                                                                                                                                                 | 
_____
 
_____
 |
| 
7. Limb Ataxia: This item is aimed at finding evidence of a unilateral cerebellar lesion. Test with eyes open. In case of visual defect, ensure testing is done in intact visual field. The finger-nose-finger and heel-shin tests are performed on both sides, and ataxia is scored only if present out of proportion to weakness. Ataxia is absent in the patient who cannot understand or is paralyzed. Only in the case of amputation or joint fusion, should the examiner record the score as untestable (UN), and clearly write the explanation for this choice. In case of blindness, test by having the patient touch nose from extended arm position.
                                                                                                                                                                                                                                               | 
0 = Absent.
 
1 = Present in one limb.
 
2 = Present in two limbs.
 
UN= Amputation or joint fusion; explain: _____
                                                                                                                                                                                                                                                                                                                                                                                                                                                                                                                                                                                                                                                                                                                                  | 
_____
 
_____
 |
| 
8. Sensory: Sensation or grimace to pinprick when tested, or withdrawal from noxious stimulus in the obtunded or aphasic patient. Only sensory loss attributed to stroke is scored as abnormal and the examiner should test as many body areas (arms (not hands), legs, trunk, face) as needed to accurately check for hemisensory loss. A score of 2, "severe or total sensory loss," should only be given when a severe or total loss of sensation can be clearly demonstrated. Stuporous and aphasic patients will, therefore, probably score 1 or 0. The patient with brainstem stroke who has bilateral loss of sensation is scored 2. If the patient does not respond and is quadriplegic, score 2. Patients in a coma (item 1a=3) are automatically given a 2 on this item.
                                                                                                                           | 
0 = Normal; no sensory loss.
 
1 = Mild-to-moderate sensory loss; patient feels pinprick is less sharp or is dull on the affected side, or there is a loss of superficial pain with pinprick, but patient is aware of being touched.
 
2 = Severe to total sensory loss; patient is not aware of being touched in the face, arm, and leg.
                                                                                                                                                                                                                                                                                                                                                                                                                                                                                                                        | 
_____
              |
| 
9. Best Language: A great deal of information about comprehension will be obtained during the preceding sections of the examination. For this scale item, the patient is asked to describe what is happening in the attached picture, to name the items on the attached naming sheet and to read from the attached list of sentences. Comprehension is judged from responses here, as well as to all of the commands in the preceding general neurological exam. If visual loss interferes with the tests, ask the patient to identify objects placed in the hand, repeat, and produce speech. The intubated patient should be asked to write. The patient in a coma (item 1a=3) will automatically score 3 on this item. The examiner must choose a score for the patient with stupor or limited cooperation, but a score of 3 should be used only if the patient is mute and follows no one-step commands.
 | 
0 = No aphasia; normal.
 
1 = Mild-to-moderate aphasia; some obvious loss of fluency or facility of comprehension, without significant limitation on ideas expressed or form of expression. Reduction of speech and/or comprehension, however, makes conversation about provided materials difficult or impossible. For example, in conversation about provided materials, examiner can identify picture or naming card content from patient's response.
 
2 = Severe aphasia; all communication is through fragmentary expression; great need for inference, questioning, and guessing by the listener. Range of information that can be exchanged is limited; listener carries burden of communication. Examiner cannot identify materials provided from patient response.
 
3 = Mute, global aphasia; no usable speech or auditory comprehension.
 | 
_____
              |

## NIHSS page 3

| Instructions                                                                                                                                                                                                                                                                                                                                                                                                                                                                                                                                                                                                                                                                                                                                                                                 | Scale Definition                                                                                                                                                                                                                                                                                                                                                                                                                                                                                                                                                                                         | Score                     |
|----------------------------------------------------------------------------------------------------------------------------------------------------------------------------------------------------------------------------------------------------------------------------------------------------------------------------------------------------------------------------------------------------------------------------------------------------------------------------------------------------------------------------------------------------------------------------------------------------------------------------------------------------------------------------------------------------------------------------------------------------------------------------------------------|----------------------------------------------------------------------------------------------------------------------------------------------------------------------------------------------------------------------------------------------------------------------------------------------------------------------------------------------------------------------------------------------------------------------------------------------------------------------------------------------------------------------------------------------------------------------------------------------------------|---------------------------|
| 
1c. LOC Commands: The patient is asked to open and close the eyes and then to grip and release the non-paretic hand. Substitute another one step command if the hands cannot be used. Credit is given if an unequivocal attempt is made but not completed due to weakness. If the patient does not respond to command, the task should be demonstrated to him/her (pantomime), and the result scored (i.e., follows none, one or two commands). Patients with trauma, amputation, or other physical impediments should be given suitable one-step commands. Only the first attempt is scored.
                                                                                                                                                                                  | 
0 = Answers both tasks correctly.
 
1 = Answers one task correctly.
 
2 = Answers neither task correctly.
                                                                                                                                                                                                                                                                                                                                                                                                                                                          | 
_____
 
_____
 |
| 
2. Best Gaze: Only horizontal eye movements will be tested. Voluntary or reflexive (oculocephalic) eye movements will be scored, but caloric testing is not done. If the patient has a conjugate deviation of the eyes that can be overcome by voluntary or reflexive activity, the score will be 1. If a patient has an isolated peripheral nerve paresis (CN III, IV or VI), score a 1. Gaze is testable in all aphasic patients. Patients with ocular trauma, bandages, pre-existing blindness, or other disorder of visual acuity or fields should be tested with reflexive movements, and a choice made by the investigator. Establishing eye contact and then moving about the patient from side to side will occasionally clarify the presence of a partial gaze palsy.
 | 
0 = Normal.
 
1 = Partial gaze palsy; gaze is abnormal in one or both eyes, but forced deviation or total gaze paresis is not present.
 
2 = Forced deviation, or total gaze paresis not overcome by the oculocephalic maneuver.
                                                                                                                                                                                                                                                                                                                                   | 
_____
              |
| 
3. Visual: Visual fields (upper and lower quadrants) are tested by confrontation, using finger counting or visual threat, as appropriate. Patients may be encouraged, but if they look at the side of the moving fingers appropriately, this can be scored as normal. If there is unilateral blindness or enucleation, visual fields in the remaining eye are scored. Score 1 only if a clear-cut asymmetry, including quadrantanopia, is found. If patient is blind from any cause, score 3. Double simultaneous stimulation is performed at this point. If there is extinction, patient receives a 1, and the results are used to respond to item 11.
                                                                                                                        | 
0 = No visual loss.
 
1 = Partial hemianopia.
 
2 = Complete hemianopia.
 
3 = Bilateral hemianopia (blind including cortical blindness).
                                                                                                                                                                                                                                                                                                                                                                                                              | 
_____
 
_____
 |
| 
4. Facial Palsy: Ask – or use pantomime to encourage – the patient to show teeth or raise eyebrows and close eyes. Score symmetry of grimace in response to noxious stimuli in the poorly responsive or non-comprehending patient. If facial trauma/bandages, orotracheal tube, tape or other physical barriers obscure the face, these should be removed to the extent possible.
                                                                                                                                                                                                                                                                                                                                                                                              | 
0 = Normal symmetrical movements.
 
1 = Minor paralysis (flattened nasolabial fold, asymmetry on smiling).
 
2 = Partial paralysis (total or near-total paralysis of lower face).
 
3 = Complete paralysis of one or both sides (absence of facial movement in the upper and lower face)
                                                                                                                                                                                                                                                               | 
_____
              |
